## Abstract

**Background:**

Upper extremity motor impairment is a prevalent and disabling consequence of stroke. While conventional rehabilitation improves function, recovery often plateaus. Cerebellar transcranial direct current stimulation (c-tDCS) presents a promising neuromodulatory adjunct by targeting cerebellar involvement in motor coordination, timing, and learning. However, robust evidence from well-designed randomized controlled trials (RCTs) is needed to establish its efficacy in enhancing post-stroke upper limb recovery.

**Objective:**

This RCT protocol aims to evaluate the efficacy of anodal c-tDCS applied sequentially with conventional upper limb rehabilitation (CULR), compared to sham stimulation plus the same rehabilitation, on improving motor function of the paretic upper extremity in subacute/chronic stroke patients.

**Methods:**

A double-blind, randomized, sham-controlled trial will be conducted. Fourty-eight participants with unilateral stroke and moderate to severe upper limb motor impairment will be randomized to either active or sham group. Anodal tDCS will be conducted to the ipsilesional cerebellar hemisphere in the active group, while sham delivery will be performed in the sham group. Both groups receive CULR after each c-tDCS session. Multimodal assessments will be administered pre- and post-intervention, comprising: Fugl-Meyer assessment upper extremity (FMA-UE) for motor impairment quantification, functional near-infrared spectroscopy (fNIRS) capturing resting-state and c-tDCS-induced cortical hemodynamic responses and transcranial magnetic stimulation-derived motor evoked potentials (TMS-MEPs) evaluating cortical excitability.

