### Participants

#### Sample size

Based on an F-test (ANOVA) with the following parameters: a conservative effect size [*f* = 0.4, based on a meta-analysis of tDCS studies for post-stroke UE recovery (13)], *α* error probability = 0.05, power (1-*β*) = 0.95, numerator df = 1, number of groups = 2, the total sample size is calculated in G-power. Accounting for an anticipated 20% attrition rate, the final required sample size is 70 participants, with 35 in each of the two groups.

**Experimental group:** Patients who receive active tDCS for 10 consecutive days with 20 min each day.**Control group:** Patients who receive sham tDCS.

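### The abstract says 48 participants will be randomised and the sample-size section requires 70, so the enrolment target is ambiguous

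*Protocol article*

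**What the plan says.** The Methods paragraph of the abstract gives the number to be randomised: "Fourty-eight participants with unilateral stroke and moderate to severe upper limb motor impairment will be randomized to either active or sham group". It gives no derivation, split by arm or attrition allowance for that number.

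The Sample size section under Participants gives a different total, with its inputs. The calculation is introduced as "Based on an F-test (ANOVA) with the following parameters". The effect size f is "0.4, based on a meta-analysis of tDCS studies for post-stroke UE recovery", the alpha is given as "error probability = 0.05", and the power and design entries are "0.95, numerator df = 1, number of groups = 2". The section then concludes: "Accounting for an anticipated 20% attrition rate", "the final required sample size is 70 participants, with 35 in each of the two groups". It names G*Power as the software but not the ANOVA procedure chosen within it.

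The Statistical analysis section plans a mixed ANOVA with group (two levels) and time (T0, T1, T2), and tests their interaction.

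**The concern.** Both figures describe the randomised total of the same trial, and both are current text. They differ by 22 participants, which is 24 against 35 per arm under equal allocation. Nothing in the article calls 48 the number of completers, a first stage or a replaced target.

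The article describes no interim look and no other rule for closing enrolment, so the planned total is what ends the trial. With two published totals, closing at 48 and continuing to 70 could each be presented afterwards as following the plan. The choice also changes the power, so the sample-size justification may not describe the trial that is actually run.

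**Working it through.** **Inputs.** From the abstract: 48 randomised. From the Sample size section: 70 randomised (35 per arm), f = 0.4, alpha = 0.05, power 0.95, numerator df 1, two groups, attrition 20%. Not stated, and so assumed where needed: the G*Power procedure, the number of measurements m, and the correlation ρ between repeated measurements.

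**Step 1. Does attrition link the two totals?**
- From 70 down: 70 × 0.8 = 56 completers; or, if the inflation was by multiplication, 70 / 1.2 = 58.3.
- From 48 up: 48 / 0.8 = 60 randomised; or 48 × 1.2 = 57.6.

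None of these gives the other figure.

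**Step 2. Can the plan's 70 be reproduced?** Power is the upper tail of a noncentral F with df 1 and N − 2.
- One-way ANOVA, noncentrality λ = f²N. Power of 0.95 needs N = 84 (λ = 0.16 × 84 = 13.44, power 0.952). With attrition this is 84 / 0.8 = 105, or 84 × 1.2 = 100.8, rounded up to 101. It does not give 70.
- Repeated-measures between-factors ANOVA, λ = f²Nm / (1 + (m − 1)ρ). With m = 3 and ρ = 0.5, N = 58 (λ = 0.16 × 58 × 3 / 2 = 13.92, power 0.956). Then 58 × 1.2 = 69.6, rounded up to 70; by division, 58 / 0.8 = 72.5, rounded up to 73. So 70 is reached, but only with an unstated m and ρ and with inflation by multiplication.
- Within-between interaction procedure, ρ = 0.5: N = 18 with three measurements or 24 with two, which is 22 to 30 after either inflation. It explains neither 48 nor 70.

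No variant tried at f = 0.4 and power 0.95 gives 48.

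**Step 3. Power for each total after 20% attrition.** Completers: 48 × 0.8 = 38.4, taken as 38; 70 × 0.8 = 56.

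| Reading | 48 randomised, 38 completers | 70 randomised, 56 completers |
|---|---|---|
| One-way ANOVA | λ = 6.08, power 0.670 | λ = 8.96, power 0.836 |
| Between-factors, m = 3, ρ = 0.3 | λ = 11.40, power 0.907 | λ = 16.80, power 0.980 |
| Between-factors, m = 3, ρ = 0.5 | λ = 9.12, power 0.836 | λ = 13.44, power 0.949 |
| Between-factors, m = 3, ρ = 0.7 | λ = 7.60, power 0.765 | λ = 11.20, power 0.908 |

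With no attrition at all, 48 gives 0.774 one-way, and 0.960, 0.913 and 0.858 for ρ = 0.3, 0.5 and 0.7.

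**The case against.** The strongest reply is that this is an abstract that was not brought into line with the body. The Sample size section is the place for the number. It gives one explicit total with inputs, an attrition allowance and a split by arm, while the abstract's 48 has no support anywhere. Much of this stands. A reader might infer that the trial has no defined end of enrolment, and the article does not support that: read alone, the Sample size section fixes 70. What remains is that the abstract is equally current and says how many will be randomised, and the article does not say which figure governs.

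A second reply concerns the power figures. A reader who applies the one-way formula might conclude that neither total delivers 95%. The article does not support that as a flat statement. It does not name the procedure, and numerator df 1 with two groups also fits a repeated-measures between-factors calculation. With three measurements and a correlation of 0.5, that calculation leads to 70 and gives about 95% with 56 completers. This reply also stands, so the power must be shown as a range. It does not rescue 48.

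A reader might also suspect selective stopping, or guess at an older calculation behind the 48. Neither can be shown: no interim analysis is described, participants and outcome assessors are blinded, and the article gives no source for the 48.

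**Conclusion.** The point holds as an internal contradiction: one of the two totals is wrong as written, and the article does not say which. The stopping number is ambiguous between 48 and 70; it is not absent.

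At f = 0.4, alpha 0.05 and 20% attrition, the choice of 48 instead of 70 costs about 17 percentage points under the one-way reading (67% against 84%). It costs about 11 points under the between-factors reading with three measurements and ρ = 0.5 (84% against 95%). A target of 48 misses 95% under every reading in the table. A target of 70 reaches about 95% only with repeated-measures assumptions that the article leaves unstated, and falls to 91% if ρ is 0.7.

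These sizes rest on the assumed procedure, m and ρ, and on attrition being as planned. They concern a between-group comparison. The within-between interaction procedure at the same f would put both totals above 95%, but it yields neither published total. The contradiction itself needs none of these assumptions.

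**What to change.** Before any outcome is examined, decide on one randomised total. State it, with the number per arm, in both the abstract and the Sample size section, and use it for the randomisation list. Beside it, give the G*Power procedure, the number of measurements and correlation if a repeated-measures procedure was used, the way attrition was applied, and the power this total delivers after attrition. The power quoted must come from the procedure actually used; none of the figures above should simply be copied in.

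If 70 is the target, the cost is a one-line correction to the abstract plus the missing inputs. If 48 is the target, the Sample size section has to be rewritten and the stated 95% power lowered to what 48 delivers.

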**Conclusion:**

This rigorously designed RCT will provide high-level evidence on the therapeutic potential of c-tDCS as an adjunct to rehabilitation for improving upper limb motor function post-stroke. Findings will inform clinical practice regarding novel neuromodulation strategies to augment recovery.

**Clinical trial registration:**

https://www.chictr.org.cn, identifier ChiCTR2500101094.

## Introduction

Stroke represents the leading cause of adult disability worldwide, imposing substantial socioeconomic burdens (1). With approximately 14 million incident strokes annually, up to 75% of survivors experience chronic disabilities (2). Upper extremity (UE) motor impairment persists as a particularly debilitating sequela, significantly compromising activities of daily living (ADL) and quality of life (3).

Post-stroke UE dysfunction stems from complex pathophysiological mechanisms, including imbalanced interhemispheric inhibition, characterized by contralesional M1 hyperexcitability suppressing ipsilesional cortex via transcallosal pathways, and disrupted cerebello-thalamo-cortical (CTC) integration (4, 5). A critical manifestation of CTC disruption is crossed cerebellar diaschisis (CCD), a biomarker associated with poorer motor recovery prognoses (6). These neural network dysfunctions collectively constrain neuroplasticity and limit functional recovery.

While conventional neurorehabilitation (e.g., task-oriented training, neuromuscular electrical stimulation, mirror therapy, robot-assisted therapy or brain-computer interface) yields partial improvements in gross motor function, efficacy for restoring fine motor control (precision grasp, bimanual coordination) and therapeutic sustainability remains limited (7–10). Non-invasive brain stimulation (NIBS), particularly transcranial direct current stimulation (tDCS), offers promise by modulating cortical excitability and enhancing neuroplasticity (11). However, optimal stimulation targets and polarities for UE recovery, especially concerning fine motor function, are inadequately characterized, and the underlying neural mechanisms require elucidation through multimodal assessment.

The cerebellum is integral to motor coordination, timing, and error correction via reciprocal connections with cortical motor areas. Cerebellar tDCS (c-tDCS) presents a compelling neuromodulatory tool. Critically, c-tDCS can modulate bilateral M1 excitability – potentially reducing pathological contralesional hyperexcitability while facilitating ipsilesional activity – thereby promoting restoration of interhemispheric balance (12). This mechanism is especially relevant given the frequent disruption of corticocerebellar pathways post-stroke.

In designing this trial, we selected anodal tDCS applied to the ipsilesional cerebellum over cathodal stimulation of the contralesional cerebellum based on a multi-faceted rationale. Firstly, the stroke lesion and its associated white matter damage likely compromise the cerebello-thalamo-cortical pathway within the affected hemisphere. In contrast, the pathway originating from the contralesional cerebellum remains relatively intact. Therefore, taking advantage of the ipsilesional cerebellum with this intact CTC pathway represents a more safe strategy for promoting recovery. Secondly, emerging evidence suggests that unilateral anodal c-tDCS can exert bidirectional effects on the bilateral motor cortices. Specifically, a study by Shoaib et al. (12) demonstrated in healthy adults that anodal stimulation of the right cerebellum significantly increased cortical activity (reflected by oxyhemoglobin concentration) in the ipsilateral right M1 while simultaneously decreasing activity in the contralateral left M1. This pattern of simultaneous ipsilateral facilitation and contralateral inhibition is ideally suited to counteract the pathological interhemispheric imbalance post-stroke. Thirdly, the rationale for inhibiting the contralesional cerebellum via cathodal tDCS is theoretically less sound. The phenomenon of CCD already indicates a state of functional depression and metabolic hypoactivity in the cerebellar hemisphere contralateral to the cerebral lesion. Applying further inhibitory stimulation to a potentially already suppressed cerebellum may not be physiologically justified, and the effects of cerebellar cathodal tDCS are generally less predictable.

Therefore, this randomized controlled trial aims to evaluate the clinical efficacy of anodal c-tDCS applied to the ipsilesional cerebellar hemisphere, combined with conventional upper limb rehabilitation (CULR), versus sham c-tDCS with CULR, for improving UE motor function in subacute/chronic stroke patients. The primary outcome is the Fugl-Meyer Assessment for the UE (FMA-UE). Furthermore, we aim to elucidate the neurophysiological mechanisms underlying c-tDCS using fNIRS to assess cortical hemodynamic activity pre-, intra-, and post-stimulation. Last but not least, we aim to employ transcranial magnetic stimulation to quantify corticospinal excitability via motor evoked potentials (MEPs) from bilateral M1.

### Hypotheses

We hypothesize that: (1) Participants receiving active anodal c-tDCS combined with CULR will demonstrate significantly greater improvement in UE motor function compared to those receiving sham c-tDCS with CULR. (2) Active c-tDCS will induce greater normalization of cortical hemodynamics, as measured by fNIRS, characterized by a shift in the laterality index. (3) Active c-tDCS will modulate corticospinal excitability, leading to increased MEP amplitudes from the ipsilesional M1 and a more balanced interhemispheric MEP ratio.

## Methods and design

### Study design

The study follows a randomized controlled trial design to examine the efficacy of c-tDCS in improving post-stroke UE motor function and the underlying cortical physiological dynamics will be characterized (Figure 1).

**Figure 1 fig1:**
[figure not shown]
Experimental flow.

### Study setting

The study is conducted at the Department of Rehabilitation Medicine, Fifth Affiliated Hospital of Guangzhou Medical University in China. Participants are recruited from the inpatient ward, and all interventions are delivered within the department by the hospital staff.

### Recruitment

Patients admitted to the inpatient ward will receive eligibility screening during regular assessment. The clinical team identifies suitable candidates and provides them with written study information. A member of the research team will then approach potential participants, explains the study in detail, and obtains written informed consent from those willing to join. A screening log is maintained to document non-recruited patients and their reasons for exclusion.

### Ethics

Data collection will be performed according to the World Medical Association Declaration of Helsinki. The study has received ethical approval from the Ethics Committee of the Fifth Affiliated Hospital, Guangzhou Medical University (GYWY-L2025-49). Additionally, the study is registered in the Chinese Clinical Trial Registry (Registration No.: ChiCTR2500101094, registered on 21 April 2025). Any significant modifications to the study protocol will be communicated to all relevant parties.

### Participants

#### Sample size

Based on an F-test (ANOVA) with the following parameters: a conservative effect size [*f* = 0.4, based on a meta-analysis of tDCS studies for post-stroke UE recovery (13)], *α* error probability = 0.05, power (1-*β*) = 0.95, numerator df = 1, number of groups = 2, the total sample size is calculated in G-power. Accounting for an anticipated 20% attrition rate, the final required sample size is 70 participants, with 35 in each of the two groups.

**Experimental group:** Patients who receive active tDCS for 10 consecutive days with 20 min each day.**Control group:** Patients who receive sham tDCS.

#### Randomization and blinding

This study will adhere to the CONSORT guidelines for randomized controlled trials (14). A computer-generated block randomization sequence (with varying block sizes) will be created by an independent statistician not involved in participant recruitment or assessment. The allocation sequence will be concealed in sequentially numbered, opaque, sealed envelopes. After obtaining baseline assessments (T0), a research assistant not involved in the study will open the next envelope to assign the participant to either the active or sham group.

This is a double-blind trial. Participants, the outcome assessors (who perform the FMA-UE, fNIRS, and TMS assessments), and the occupational therapists delivering the conventional rehabilitation will be blinded to group assignment. The investigator responsible for setting up and initiating the tDCS device will not be blinded, as they must input the correct stimulation code (active/sham) for the device. However, this investigator will have no role in outcome assessment or data analysis.

#### Experimental procedure

Eligible participants with unilateral upper extremity motor impairment will be formally screened by a qualified rehabilitation physician according to the predefined inclusion/exclusion criteria (Table 1). Participants will be assigned randomly to the active or sham tDCS group after written informed consent is obtained. The detailed experimental workflow is outlined in Figure 1.

**Table 1 tab1:** Inclusion and exclusion criteria.

Inclusion criteria	Exclusion criteria
1. Diagnosis of a first-ever, unilateral, supratentorial ischemic or hemorrhagic stroke, confirmed by CT or MRI;	1. Current pregnancy, lactation or gestation
2. Post-stroke chronicity ranging from 1 week to 2 years;	2. Concurrent participation in clinical trials within the preceding 3 months
3. Ability to maintain assisted sitting posture for ≥40 min without distress;	3. Any clinically significant condition or circumstance deemed by the Principal Investigator to compromise participant safety or protocol adherence at any study phase.

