**Figure 2 fig2:**
[figure not shown]
Assessments and interventions.

**Table 2 tab2:** Schedule of assessments and outcome measures.

Domain	Outcome measure	Specific variables	Timepoint
Primary	FMA-UE	Total score (0–66)	T0, T1, T2
Secondary	fNIRS	HbO/HbR concentration, Laterality Index (LI)	T0, T1, T2
	TMS-MEP	RMT, MEP Amplitude, MEP Latency, Interhemispheric Ratio	T0, T1, T2
Other	Demographics and clinical data	Age, sex, stroke type, lesion location, time since stroke, etc.	T0

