## Outcomes

### Primary outcomes

The FMA-UE is a standardized clinical evaluation tool focusing on motor function of the upper extremity (15), comprising 33 assessment items. This scale employs a 3-point scoring criterion (0 = cannot perform; 1 = partially performs; 2 = fully performs), with a total score range of 0–66, where higher scores indicate better motor function (16). Previous studies have demonstrated its excellent validity and reliability (16), establishing it as a robust instrument for assessing post-stroke upper extremity motor impairment. The application of FMA-UE in this study aims to evaluate the clinical efficacy of tDCS targeting the cerebellum in improving upper extremity function after stroke. A change of ≥ 4.25–5.25 points on the FMA-UE will be considered the minimal clinically important difference (MCID) for interpreting the results, based on established values for the stroke population.

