### Statistical analysis

The primary analysis will follow the Intention-to-Treat (ITT) principle, including all randomized participants in the groups to which they were originally assigned. For the primary outcome (FMA-UE), missing data will be handled using multiple imputation. A per-protocol (PP) analysis will also be conducted as a sensitivity analysis. To test the primary hypothesis, a mixed-model Analysis of Variance (ANOVA) with factors for Group (active, sham) and Time (T0, T1, T2) will be used to test for the crucial Group x Time interaction effect.

Descriptive statistics will be employed to characterize participants’ clinical profiles. Between-group comparisons will be performed using chi-square tests for categorical variables and independent samples t-tests for continuous variables. Prior to parametric testing, data normality and variance homogeneity will be assessed using the Kolmogorov–Smirnov test and Levene test in the SPSS. All statistical analyses will be performed using SPSS software (version 20.0; SPSS Inc., Chicago, IL, USA). A *p*-value <0.05 will be considered as statistically significant. In addition to the primary analysis, exploratory subgroup analyses will be conducted based on baseline impairment severity (FMA-UE score: moderate [20–40] vs. severe [0–19]) to investigate potential differential treatment effects.

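### Time since stroke ranges from 1 week to 2 years and is recorded at T0, but the stated primary model leaves it out, which costs precision and power

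*Protocol article*

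**What the plan says.** Table 1 of the protocol article admits patients with "Post-stroke chronicity ranging from 1 week to 2 years". Under Randomization and blinding, allocation is described as follows: "A computer-generated block randomization sequence (with varying block sizes) will be created by an independent statistician". No stratification factor is named there.

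Table 2 lists time since stroke among the baseline data taken at T0: "Age, sex, stroke type, lesion location, time since stroke, etc". The Statistical analysis section gives it no role. The primary test is a mixed ANOVA in which "factors for Group (active, sham) and Time (T0, T1, T2) will be used to test for the crucial Group x Time interaction effect", and no covariate is named. The only planned subgrouping is by severity: "exploratory subgroup analyses will be conducted based on baseline impairment severity" (FMA-UE 0–19 against 20–40). Severity is not named as a randomisation factor either.

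For scale, the Primary outcomes section states that a change of at least "4.25–5.25 points on the FMA-UE will be considered the minimal clinically important difference (MCID").

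**The concern.** The article itself says that recovery often plateaus, and it describes its population as subacute/chronic. With 10 days of treatment and a one-month follow-up, a patient enrolled at week 1 is observed over roughly the first two months after stroke. A patient enrolled near 2 years is observed long after that. The two can be expected to gain FMA-UE points at different rates whatever the arm.

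The repeated-measures model removes differences in baseline level between patients. It does not remove differences in slope, and Group x Time is a test of slopes. Variation in recovery that a recorded variable could partly explain is therefore left as noise. In a trial of 48 to 70 patients this matters mainly for power, and for how a result would be read if the arms happened to differ in time since stroke.

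**Working it through.** **Inputs from the documents.** Sample size section: 35 per arm, 20% attrition, f = 0.4 (for two equal groups d = 2f = 0.8). So 35 × 0.8 = 28 analysed per arm. The Abstract gives 48 in total, or 24 per arm. MCID: 4.25–5.25 points.

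**Inputs that are assumed.** Share of early patients p = 0.5; extra FMA-UE gain of early over late patients during the study D = 5 to 10 points; SD of change within each class s = 6 to 8. None of these is in the documents.

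**The plan's own figure.** The plan gives none for time since stroke. Its sample size of 70 is not reproduced: a two-group F-test with the stated inputs needs 84 analysed, or 84/0.8 = 105 after attrition. That, and the conflict between 48 and 70, are separate points. Only the arm sizes and d = 0.8 are used here.

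**Chance shift.** The difference between arms in the early share has SD = √(2p(1−p)/n) = √(2 × 0.25/28) = 0.134. A simulation with permuted blocks of 4 gives 0.133, so blocks without strata do not narrow it. The 95% bound of the resulting shift is 1.96 × 0.134 × D:

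- D = 5: ±1.3 points
- D = 10: ±2.6 points

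Against the MCID this runs from 1.31/5.25 = 25% to 2.62/4.25 = 62%. With p = 0.3 the bounds are ±1.2 and ±2.4 points.

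**Variance.** The ratio is (s² + p(1−p)D²)/s²:

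- s = 6: (36 + 6.25)/36 = 1.17 for D = 5; (36 + 25)/36 = 1.69 for D = 10
- s = 8: (64 + 6.25)/64 = 1.10 for D = 5; (64 + 25)/64 = 1.39 for D = 10

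**One effect, two descriptions.** The extra variance per patient, p(1−p)D², contributes p(1−p)D² × 2/n to the variance of the group difference. That is exactly the square of D × √(2p(1−p)/n), the SD of the chance shift. The two figures must not be added together.

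**Power.** Here the group comparison of change is treated as a two-group test, and the MCID is taken to equal d = 0.8 within a class. That gives s = 4.25/0.8 = 5.3 to 5.25/0.8 = 6.6. With D = 10 the total SD becomes √(5.3² + 25) = 7.3 to √(6.6² + 25) = 8.3, and d falls to 0.58–0.64.

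| Analysed per arm | No gap, or gap fully adjusted for | D = 5, unadjusted | D = 10, unadjusted |
|---|---|---|---|
| 35 | 91% | 85–87% | 67–75% |
| 28 | 84% | 76–78% | 57–65% |
| 24 | 77% | 69–72% | 51–58% |

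**When would the shift reach the MCID?** With 28 per arm the 95% bound equals 4.25 when D = 4.25/(1.96 × 0.134) = 16.2 points. The corresponding gap is 15.0 with 24 per arm and 18.1 with 35. At D = 10 and 28 per arm, a shift of 4.25 or more in either direction has probability 0.15%.

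**The case against.** Four objections deserve an answer.

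- **Scope.** Covariates and stratification details are often left to a full protocol or SAP, and neither is shown. This stands for stratification: the article is silent on it, and silence does not prove that the blocks are unstratified. It has less force for the model, because the article does state the model and its factors, and time since stroke is not among them.
- **Intended population.** Enrolling both subacute and chronic patients is the trial's stated aim. This stands, and nothing here asks for a narrower window.
- **Assumed size.** Every driver of the magnitude is assumed, and p = 0.5 is the value that maximises p(1−p). Recruitment from an inpatient ward does not suggest an even split. This stands, so the figures are a range under stated assumptions and not an estimate.
- **Validity.** Randomisation keeps the unadjusted comparison unbiased, and its standard error already contains this variance. This also stands. A reader might infer that the wide window biases the result or inflates the type I error; the documents do not support that.

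**Conclusion.** The point holds as one of efficiency. A recorded baseline variable that is probably prognostic for change has no role in the stated primary analysis, so differing recovery slopes remain in the error term of the Group x Time test. Under the assumptions above (half early, gap 5–10 points, 28 per arm), the 95% chance shift is about ±1.3 to ±2.6 points, or equivalently the variance of change rises by a factor of 1.10 to 1.69. Power at that size falls from 84% to somewhere between 57% and 78%.

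A reader might go further and say that chance imbalance can rival the MCID. The figures do not bear that out: it would take a gap of about 15 to 18 points together with an imbalance at the edge of its 95% range, and nothing in the documents indicates a gap of that size.

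**What to change.** Before unblinding, pre-specify one of two forms of the primary analysis:

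1. A baseline-adjusted model of FMA-UE at T1 and T2, with Group, Time, Group x Time, T0 FMA-UE, log time since stroke, and log time since stroke x Time. T0 must then be a covariate only and no longer a level of the outcome; otherwise it stands on both sides of the model. The treatment effect becomes the adjusted group difference at T1 and T2, and the plan should say so, because Group x Time would then test only whether that difference changes between T1 and T2.
2. The stated mixed model with T0 kept as an outcome level, plus time since stroke and time since stroke x Time. A main effect alone would adjust the average level and leave the Group x Time test as it is.

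Either form uses data already listed in Table 2 and costs about two degrees of freedom for time since stroke. The power recovered depends on how well time since stroke predicts change; the fully adjusted column in the table is the best case.

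Stratifying envelopes not yet opened by time since stroke is optional. It needs a pre-specified cut, because the article uses the term subacute/chronic without stating a boundary. Adding severity as a second factor would make four cells averaging 12 (48/4) to 17.5 (70/4) patients, where incomplete blocks can erode the balance sought, so the gain there is debatable.
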